### Study Design and Sample Size Determination

The sample size was determined using standard parameters (*α*=.05, 2-sided tests), based on the primary end point and allowing for the detection of a 15 percentage point improvement in the primary end point, our minimum threshold to consider the C3Link package of strategies to be successful. For the enhanced standard-of-care arm, given the current low level of screening, we estimated the screening uptake for both cancers to be about 15% at the 24-month follow-up (end of intervention phase). With a sample size of 100 in each of the 9 communities in the trial arms (for a total of 2700 women, and each woman will select 1 family member or support person), we will be able to detect a 15% difference with over 80% power, even after accounting for up to 20% attrition at 24 months. We selected a screening uptake of at least 30% in either the C3Link Core or Plus arm on the basis of prior study results [62,63]. We estimate that the interclass correlation coefficient would be in the range of 0.03 to 0.05 because interclass correlation coefficients for binary data are typically quite small, especially when screening uptake is very low [64]. Furthermore, we anticipate that the C3Link Plus arm would achieve a higher uptake than the C3Link Core arm, and we would be able to detect any difference of 15 percentage points between this study’s arms (ie, screening uptake of 15%, 30%, and 45% in the enhanced standard-of-care, C3Link Core, and C3Link Plus arms, respectively) with over 90% power. In each community, we will select study participants, 1 woman per household, using the Kish method [65], with eligibility remaining the same as previously stated. We will oversample by 10% to account for participants who cannot be contacted, refuse to participate, or are no longer eligible. The C3Link study cluster randomization is presented in Figure 2.

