### Data Analysis

Hypothesis testing will be carried out by intent to treat, and we will examine the effects at the individual level across the 3 randomization groups. We will use generalized estimating equation models to estimate the effects of the randomization groups. If the Hausman assumption of correlation between the random and fixed effects is violated, then we will include fixed effects representing cluster identification [71]. We will adjust for baseline covariates, including sociodemographic and behavioral factors, should the initial descriptive analyses suggest differences in the distribution of these factors across study randomization groups. We will also explore the use of propensity scores to control for systematic differences between the groups. In further analyses, we will compare differences in mediating outcomes across the groups and examine the potential moderating roles of key individual behavioral, social, and structural factors hypothesized to influence cancer screening and adherence along the cancer care continuum, as shown in Figure 1. We will test the “dose” of the C3Link Core and Plus strategies received as a covariate in these models. We will explore differences in breast and cervical cancer screening completion and report the proportion that complete at least one of the screenings. As appropriate, we will perform analyses separately or pooled together for the younger and older cohorts of women to assess whether care-seeking behavior differs by age group. A key aspect of interest in this study is the extent to which perceived and anticipated stigma affects care-seeking behavior and screening completion. In subsequent analyses, we will consider both medium-term outcomes within the first 12 months after enrollment and changes at any point during the 24-month and 36-month follow-up period to assess longer-term outcomes. To understand potential variation across communities, we will conduct comparisons to analyze differences in mediating and screening outcomes among each of the C3Link Core and Plus communities. We will also report on the overall quality of the screenings provided, women’s preferences for cervical cancer screening, and the type of procedures used along the continuum of care. For the C3Link Plus arm, we will document the increase in screening completion with each step in the series of individual strategies and the number of women requiring each type of strategy.

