Although cluster randomization reduces contamination across study arms, it increases the risk that women in each arm may differ at baseline. This study’s sampling frame will allow us to assess baseline differences before randomization and adjust our sampling process with propensity score weighting methods. Second, data could be missing because of nonresponse and study attrition. This study’s CHWs in each community will maintain regular contact with the women, and we will also use rigorous field data collection practices, including training data collectors, developing protocols, and monitoring fidelity continually. To limit missing data, we will train clinic staff and data collectors and implement continuous quality review. Furthermore, we will address any missing data by including demographic covariates that will serve as proxies for dropout and conducting sensitivity analyses.

We will select 1 eligible woman from within each household in the selected communities. To reduce interviewer bias, we will use the Kish method to provide a random and consistent procedure for women’s selection.

A key constraint in implementing strategies in low- and middle-income countries is funding. This is the first cancer screening study in Kenya, and to our knowledge, in any other limited-resource setting, that will evaluate implementation strategies in a predetermined sequence and assess effectiveness and cost at each step. This will allow us to determine the incremental cost-effectiveness of each strategy in the sequence to guide policy. For example, given the available resources and cost-effectiveness profile, a Kenyan county may decide to implement C3Link Core with only the first level in the sequence of C3Link Plus. Importantly, the findings will guide future studies in testing additional combinations and sequences.

This trial features novel evidence-based strategies to increase uptake of breast and cervical cancer screening in variously resourced settings in a cost-effective process. We anticipate that the findings will be valuable not only in Kenya but also in other sub-Saharan African countries.

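### Baseline covariates should enter the outcome model as a short fixed set including clinic, not according to whether the arms look different at baseline

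*Protocol article*

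**What the plan says.** The Data Analysis section of the protocol article sets out an intention-to-treat comparison of three arms at the level of the individual woman: "We will use generalized estimating equation models to estimate the effects of the randomization groups". On covariates it says "We will adjust for baseline covariates, including sociodemographic and behavioral factors", but attaches a condition: "should the initial descriptive analyses suggest differences in the distribution of these factors across study randomization groups". The covariates are described as a class and not listed, and no test or threshold defines a difference. The next sentence opens a second route: "We will also explore the use of propensity scores to control for systematic differences between the groups".

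The Discussion (Defining Features of our Approach) returns to the subject. It says of cluster randomisation that "it increases the risk that women in each arm may differ at baseline", and that the sampling frame will let the team "assess baseline differences before randomization and adjust our sampling process with propensity score weighting methods". Under missing data it also plans on "including demographic covariates that will serve as proxies for dropout", with no imbalance condition.

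The Recruitment section says that the three communities attached to each clinic are allocated one to each arm, so clinic is the randomisation block. The Data Analysis section does not mention clinic as a model term.

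**The concern.** A covariate is worth including because it predicts the outcome. Observed imbalance is a poor guide to that. Under the stated rule, a strong predictor of screening that happens to look balanced is left out, while a weak one that looks unbalanced goes in. Because no criterion is given for what counts as a difference, two analysts following the same sentence could fit different primary models, and the choice is made after looking at the data.

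Clustering makes the condition easy to meet. Arm means of a baseline covariate vary more between arms of nine communities than they would between arms of 900 independent women, so a descriptive comparison that ignores communities will often suggest a difference where allocation was sound. The Discussion itself expects such differences. At stake are the credibility of the primary estimate as prespecified and the precision that known predictors and the randomisation block would give.

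**Working it through.** **Inputs from the protocol article (Study Design and Sample Size Determination; Recruitment).** Nine communities per arm with 100 women each ("With a sample size of 100 in each of the 9 communities in the trial arms"); outcome ICC 0.03 to 0.05; uptake 15% against 30%; two-sided α of 0.05; up to 20% attrition; allocation within clinic. **Assumed, because not given:** the covariate ICC, the flagging criterion and the R² of a covariate.

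**1. The plan's own power figure.** After attrition m = 80, so 9 × 80 = 720 women per arm. Effective n = 720 / [1 + 79 × ICC], which is 720 / 3.37 = 213.6 at ICC 0.03 and 720 / 4.95 = 145.5 at 0.05. The normal-approximation power for 15% against 30% is 0.963 and 0.869. With a t distribution on 16 degrees of freedom it is 0.943 and 0.832. The stated figure of over 80% reproduces, without any covariate adjustment.

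**2. How often a chance difference would be flagged.** For one covariate at baseline (m = 100), the design effect is DE = 1 + 99 × ICC. An unclustered two-arm 5% test flags with probability 2 × [1 − Φ(1.96 / √DE)]. An unclustered three-arm test (chi-square, 2 df, critical value 5.99) flags with probability exp(−5.99 / (2 × DE)).

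| Assumed covariate ICC | DE | Two-arm test | Three-arm test |
|---|---|---|---|
| 0 | 1.00 | 5% | 5% |
| 0.01 | 1.99 | 16% | 22% |
| 0.03 | 3.97 | 33% | 47% |
| 0.05 | 5.95 | 42% | 60% |

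A different criterion, a standardised difference above 0.1 between any two arms, gives 29%, 54% and 66% at ICC 0.01, 0.03 and 0.05, against 8.5% without clustering.

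**3. What the rule costs.** Two-arm trials were simulated (20,000 per setting; nine communities per arm, 80 women each, a linear outcome, outcome ICC 0.05, one covariate, t test on community means, no separate clinic effect). Always adjusting was compared with adjusting only if the unclustered 5% test flags the covariate. Power is for a true difference of 0.25.

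| R² | Covariate ICC | Power, always | Power, if flagged | Gap (points) | Type I, always | Type I, if flagged |
|---|---|---|---|---|---|---|
| 0.05 | 0.05 | 0.533 | 0.521 | 1.1 | 0.047 | 0.045 |
| 0.05 | 0.10 | 0.539 | 0.523 | 1.6 | 0.050 | 0.048 |
| 0.10 | 0.05 | 0.558 | 0.531 | 2.6 | 0.049 | 0.045 |
| 0.10 | 0.10 | 0.554 | 0.517 | 3.7 | 0.050 | 0.043 |
| 0.20 | 0.05 | 0.605 | 0.548 | 5.7 | 0.049 | 0.039 |
| 0.20 | 0.10 | 0.610 | 0.538 | 7.2 | 0.054 | 0.041 |

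The conditional rule has type I error of 0.039 to 0.048, slightly conservative. The power gaps were measured where power is a little over one half, where a change in precision moves power most. At the planned power they would be smaller.

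**The case against.** Several objections have force.

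- **No unclustered test is written into the plan.** The flag rates rest on an assumed criterion and assumed covariate ICCs. Because allocation is within clinic, variation between clinics is balanced by design, so the relevant ICC may lie at the low end. The percentages illustrate the problem and do not predict what will happen in this trial.
- **Imbalance here need not be chance.** A reader might infer that randomisation makes every baseline difference accidental. The documents do not support that for the enrolled women. Communities are allocated and households then visited (Recruitment). Study CHWs, who help with the visits and administer the eligibility survey, are recruited from Core and Plus communities (C3Link Community Implementation), and the comparison communities have none (Implementation Strategies). Enrolling staff may therefore have known the arm, and recruitment could have differed by arm. This is a reason to keep propensity-score methods in a secondary role.
- **Imbalance is not the only way in.** The Discussion also brings in demographic covariates as proxies for dropout. That passage handles missing data and does not set the primary adjustment.
- **An analysis plan that is not shown may hold the covariate list and the clinic term.** Their absence from an article is not in itself a fault. The conditional rule, however, is stated, and a fixed prognostic set would replace that sentence, not fill it in.
- **The Discussion sentence on assessing differences before randomisation** can be read as comparing communities from the sampling frame before allocation. On that reading it does not contradict Recruitment, so it is a side point of wording.

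**Conclusion.** The point holds as a fault in a stated rule: adjustment is triggered by observed differences, so the outcome model depends on looking at the data and may omit useful predictors. Under every criterion and positive covariate ICC examined, chance flags are well above the nominal level. The cost in precision is modest, about 1 to 3 power points at R² 0.05 to 0.10 (up to about 4 if the covariate ICC is 0.10) and 6 to 7 at R² 0.20. The R², covariate ICC and flagging criterion are all assumptions.

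A reader might infer that the rule invalidates the primary test. The calculations do not support that: with one rule fixed and followed, type I error stays at or below about 5%, and the plan's power claim stands without adjustment. The remaining concern is discretion where no rule has been fixed. This is a change that should be made; it is not a flaw that undermines the trial.

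**What to change.** Before the 24-month analysis (data collection in early 2027, per the Results section):

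- Replace the conditional sentence with a short fixed set that is always in the primary model: clinic as the randomisation block, age, and one or two baseline predictors such as socioeconomic status and baseline care-seeking. With 27 communities, and eight degrees of freedom already used by nine clinics, the set must stay short.
- Report baseline differences descriptively only, with no effect on the model.
- Keep propensity-score methods as a labelled sensitivity analysis, because women were enrolled after allocation.
- Reconcile the Discussion sentence on assessing differences before randomisation and adjusting sampling with the Recruitment section. Enrolment is complete (November or December 2024, depending on the section), so sampling can no longer be adjusted.

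The cost is wording only. Age is known from eligibility, clinic from allocation, and Table 3 lists socioeconomic status and care-seeking at baseline. No sample size or power figure changes.

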### Hypothesis Testing

We will test the following hypotheses: (1) women from communities with more evidence-based strategies (C3Link Plus followed by C3Link Core and then enhanced standard of care) will have progressively higher cancer screening uptake (completion of recommended breast and cervical screenings); (2) women from communities with C3Link Core or Plus strategies will have higher follow-up compliance with supplemental or diagnostic follow-up referrals and initiation of cancer treatment than women in the enhanced standard of care; (3) women from C3Link Plus communities will have higher completion of recommended repeat breast and cervical cancer screenings than women from C3Link Core or enhanced standard-of-care communities; and (4) women from communities that receive C3Link Core or Plus strategies will have improved self-efficacy, social support, and knowledge of cancer risk factors compared to women in the enhanced standard-of-care communities.

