Proportion of patients completing repeat screening at the recommended interval (at 36 months)	Repeat screening based on Kenya guidelines and risk profile of the women, prespecified abstraction tool	Biological, imaging, and clinical procedures identified through clinic audits and this study’s database	36 months

a HPV: human papillomavirus.

b CBE: clinical breast examination.

**Table 3. T3:** Data collection at baseline, 12 months, 24 months, and 36 months. Mediating outcomes, auxiliary end points, intervention dose, and clinic-based services.

Demographics and socioeconomic status	RTI^a^ cervical and breast cancer Kenya survey	Self-report	Baseline
Self-efficacy (women)	Generalized Self-Efficacy Scale [66]	Self-report	Baseline, 12 months, 24 months, and 36 months
Social support (women and family)	Brief Social Support Questionnaire [67], frequency of contact	Self-report	Baseline, 12 months, 24 months, and 36 months
Cancer stigma (women and family)	Perceived and anticipated [27,68]		Baseline, 12 months, 24 months, and 36 months
Cancer risk (women and family)	Breast Cancer Awareness Measure [69], RTI Kenya Survey	Self-report	Baseline, 12 months, 24 months, and 36 months
Self-care and care-seeking behavior, including wellness care (women)	Proportion conducting breast self-examination, number of visits, proportion with blood pressure and blood sugar testing	Self-report clinic audit	Baseline, 12 months, 24 months, and 36 months
Confidence in provider or system (women)	RTI Kenya survey questions on access and quality of care	Self-report	Baseline, 12 months, 24 months, and 36 months
Group education (women and family)	Number and proportion of education sessions attended (dose)	Study CHW^b^ tool study database	12, 24, and 36 months
Individual strategies (C3Link Plus only)	Number of women receiving each level of strategy (dose)	Study CHW tool study database	12, 24, and 36 months
Clinic team training sessions	Proportion of patients who attended the training sessions (dose)	Study CHW tool study database	12, 24, and 36 months
Clinic team meetings (study CHW and provider)	Number and proportion of meetings attended (dose)	Study CHW tool study database	12, 24, and 36 months
Clinic staff knowledge and attitudes (20 providers per clinic initially trained)	Tailored survey on screening quality, skills from training, and patient communication; stigma (modified Nyblade instrument) [70]	Self-report	Baseline and 24 months

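### The analysis of the Hypothesis 4 scales does not commit to using each scale's own baseline score; the only stated adjustment rule depends on observed imbalance in other factors

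*Protocol article*

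**What the plan says.** The Hypothesis Testing section states as its fourth hypothesis that women in the Core or Plus communities "will have improved self-efficacy, social support, and knowledge of cancer risk factors compared to women in the enhanced standard-of-care communities".

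Table 3 (Data Collection section) gives the schedule, for example "Generalized Self-Efficacy Scale [66] Self-report Baseline, 12 months, 24 months, and 36 months". Social support and cancer risk have the same four time points.

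The Data Analysis section makes four statements that bear on these outcomes:
- The model class: "We will use generalized estimating equation models to estimate the effects of the randomization groups".
- The comparison itself: "we will compare differences in mediating outcomes across the groups and examine the potential moderating roles" of individual, social and structural factors.
- A covariate rule: baseline covariates, with social, demographic and behavioural factors given as what they include, enter the model "should the initial descriptive analyses suggest differences in the distribution of these factors across study randomization groups".
- A possible extra: "We will also explore the use of propensity scores to control for systematic differences between the groups".

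The Discussion (Defining Features of our Approach) says of cluster randomization that "it increases the risk that women in each arm may differ at baseline", and mentions propensity score weighting as a response.

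**The concern.** When the baseline value of the same outcome is collected on every woman, it is usually the strongest available predictor of the follow-up value. Good practice is to name it in advance as a covariate, whether or not the arms look different at the start. The article instead fixes a rule under which adjustment is triggered by an observed imbalance, and the factors it names do not clearly include the scale scores.

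Two things are at stake. First, precision: with nine communities per arm, the arm contrast on each scale is driven by variation between communities, and a baseline score can remove part of it. Second, prespecification: a model that depends on what the descriptive tables show leaves the Hypothesis 4 estimate open to choice after the data are seen.

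Screening uptake differs in this respect. Enrolled women are due for both screenings, so the primary end point has no comparable baseline value. For the scales, the natural covariate is already in the database.

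**Working it through.** **Inputs from the article** (Study Design and Sample Size Determination): k = 9 communities per arm, 100 women in each, up to 20% attrition by 24 months (so m = 80), two-sided alpha 0.05, and an intracluster correlation (ICC) of 0.03 to 0.05, stated for binary screening data.

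**Assumptions**, because the article gives no figures for the scales: SD = 1; the same ICC range applies; R, the correlation of community means between baseline and follow-up, is 0.3, 0.5 or 0.7. Communities are treated as if not grouped by clinic.

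**The article's own figure.** It states over 80% power for 15% against 30% screening uptake. The effective sample size per arm is 9 × 80 / (1 + 79 × ICC): 720/3.37 = 213.6 at ICC 0.03 and 720/4.95 = 145.5 at ICC 0.05. Power is 96.3% and 86.9%, so the statement reproduces. No power is stated for the Hypothesis 4 scales.

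**Without the baseline score.** Variance of the difference between two arms = 2 × (1 + 79 × ICC) / 720.
- ICC 0.03: 2 × 3.37/720 = 0.00936, SE 0.097, detectable difference at 80% power 2.80 × SE = 0.271 SD.
- ICC 0.05: 2 × 4.95/720 = 0.01375, SE 0.117, detectable difference 0.329 SD.

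**With the baseline score in the model.** The variance is multiplied by 1 − R². At an effect that has 80% power unadjusted, power becomes Φ(2.80/√(1 − R²) − 1.96).

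| R | 1 − R² | Detectable difference (ICC 0.03 / 0.05) | Power | Variance ratio of a raw change score, 2(1 − R) |
|---|---|---|---|---|
| 0.3 | 0.91 | 0.259 / 0.313 SD | 84% | 1.4 |
| 0.5 | 0.75 | 0.235 / 0.285 SD | 90% | 1.0 |
| 0.7 | 0.51 | 0.194 / 0.235 SD | 97% | 0.6 |

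A raw change score therefore gains nothing at R = 0.5 and loses precision below that. It is less efficient than covariate adjustment at all three values.

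**Small-sample check.** These are normal approximations. A simulated regression on 18 community means with a t test puts unadjusted power at the same effect at about 75%. Adjustment raises it to about 76%, 83% and 94% at R = 0.3, 0.5 and 0.7. At R = 0.3, the lost degree of freedom absorbs most of the benefit.

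**Correlation only at the woman level.** If the woman-level correlation is 0.5 and community effects at baseline and follow-up are unrelated, the variance ratio is [ICC + (1 − ICC) × 0.75/80] / [ICC + (1 − ICC)/80]. This is 0.928 at ICC 0.03 and 0.952 at ICC 0.05. Power rises from 80% to 83% or 82%.

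**Chance imbalance at baseline.** With 100 women per community, the SD of the gap between two arms is √(2 × (ICC + (1 − ICC)/100)/9), which is 0.094 or 0.115. The 95% range is about ±0.18 or ±0.23 SD. The unadjusted standard error already carries the effect of such gaps on the follow-up comparison, so they are not a second penalty on top of it.

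**The case against.** The strongest reply is that this is silence in a condensed article. The comparison of mediating outcomes is introduced as a further analysis, and the exact covariates for it are ordinary content of a statistical analysis plan, which is not shown. The list of covariates is also open-ended, propensity scores are mentioned, and the GEE could well use the baseline visit.

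Part of this stands. A reader might infer that the scales will be compared at follow-up only and without adjustment. The text does not support that: the sentence gives no time point, the hypothesis speaks of improvement, and the section refers in general terms to changes over follow-up. A reader might also infer that the estimate would be biased. Under randomization, chance differences between communities add variance, not systematic error. Nor can a ten-point gain in power be read from the article: it requires R = 0.5, which is an assumption, and the ICC is borrowed from a binary outcome. Finally, the three communities of each clinic are split across the three arms. Variation shared within a clinic is therefore balanced, and the formulas above overstate the variance to the extent that the ICC reflects differences between clinics or counties.

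What does not stand is the claim of pure silence. The article states an adjustment rule and makes it conditional on observed imbalance. An analysis plan that followed this rule would inherit the weakness. The propensity score provisions are exploratory or again respond to observed differences, and neither names the scale scores.

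**Conclusion.** The point holds in a limited form. For the Hypothesis 4 scales, the article makes baseline adjustment depend on observed imbalance and does not commit to each scale's own baseline score, although it collects that score. The cost is precision and a data-dependent model.

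Under the assumptions above, unconditional adjustment lowers the standard error by about 5%, 13% or 29% at correlations of 0.3, 0.5 or 0.7. The benefit could be as little as 1 to 3 points of power if the correlation is low or confined to the woman level. The primary end point and its stated power are unaffected. This is a worthwhile improvement to a secondary analysis, not a flaw that threatens the trial.

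**What to change.** In the Data Analysis section, state that each Hypothesis 4 scale is analysed with its own baseline score in the model, regardless of observed imbalance, and that the arm difference from this model is the Hypothesis 4 result. Either of two forms would serve:
- a GEE or ANCOVA-type model of the follow-up scores with the woman's baseline score and the community mean baseline score as covariates; or
- a longitudinal model of all four visits with arm means constrained to be equal at baseline, which also keeps women whose baseline score is missing.

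The cost is a sentence of analysis text and one or two community-level degrees of freedom. No new data, visits or staff are needed. The 24-month analysis is planned for early 2027, so the wording can be fixed before those data are analysed.
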